### Infrared surgical navigation

After standard exposure of the region of interest of the spine a CBCT of the area is performed using the O-arm (Medtronic, Minneapolis, Minnesota, USA) and Universal Air (Brainlab spinal navigation system, Brainlab AG, Munich, Germany). Navigation is based on the recognition of optical markers on a dynamic reference frame attached to a bony prominence of the spine (Brainlab). Navigation requires detection of the optical markers through infrared light and that the reference frame is tightly fixed to the spine. The CBCT will result in a three-dimensional image of the spine in which screws are placed virtually on a computer screen. After placement of the screws, the positioning is checked with a second CBCT. Misplaced screws may be repositioned or extracted [22].

After screw placement, rods are placed, correction of the deformity and fusion are performed, and the wound is closed.

### Free hand

After standard exposure of the region of interest of the spine screws are placed based on anatomical landmarks and feeling of intact bony canals made in the pedicle [14]. If needed, fluoroscopy is performed to check the planned screw paths. After placement of the screws, the positioning is checked with a cone beam CT (O-arm or Philips Allura). Misplaced screws may be repositioned or extracted. After screw placement, rods are placed, correction of the deformity and fusion are performed, and the wound is closed.

### Study outcomes and variables

Primary and secondary study outcomes will be studied in comparisons between ARSN and free hand, IRSN and free hand, and ARSN and IRSN.

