## Abstract

**Background and purpose:**

Although navigation is increasingly used in spinal surgery, the advantage of different navigation technologies is still a matter of debate. Conventional image-guided navigation is currently the gold standard. However, modern, Augmented reality-based navigation methods are increasingly gaining ground. Surgical navigation in deformity surgery allows placement of pedicle screws in small and deformed pedicles and may result in both a higher accuracy and density of pedicle screw placement. The aim of this trial is to compare AR and conventional surgical navigation to free-hand technique.

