Most of the commercially available navigation systems are based on infrared cameras, using outside-in detection of reflective spheres on a dynamic reference frame fixed to the patient’s spine. Emerging video-based systems incorporating augmented reality (AR) for surgical navigation, along with intraoperative three-dimensional imaging, represent innovative computer-assisted navigation techniques [9–11]. These systems have demonstrated relatively high accuracy, safety, and effectiveness in previous studies reports on pedicle screw placement [4, 12, 13].

Nonetheless, as of now, the majority of data in this area is based on retrospective and a few prospectively collected series [12, 14, 15], while randomized controlled trials on spinal deformity are lacking. This is similar to the current situation of evidence on robotic pedicle screw placement, where the evidence from randomized studies comparing robotic guidance to navigation is scarce [6, 16, 17].

The aim of this trial will hence be to compare conventional and AR surgical navigation to free-hand technique based on three main study domains: implant placement accuracy, intraoperative radiation exposure and metrics, and operative time for navigation. Intraoperative adverse events will also be reported. Finally, since data on cost-effectiveness is crucial to ensure adequate allocation of healthcare resources, the cost-effectiveness of this technology will be assessed.

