### Sample size calculation

#### Sample size for primary objective

Based on our own and studies from others we estimate that accuracy at 1 st attempt in any of the navigated groups is p_nav_ = 91% and accuracy in the free hand group is p_control_ 84% [14, 28]. Consequently, a one-sided test can be used. With a power of 80%, alpha = 0.05, a sample size of 301 screws is obtained using sample size calculation for chi-squared test with continuity correction with equal group sizes. With a possible loss of data of 10% we aim for 332 screws in each group (rounded up to the closest integer).

With a mean of 15 screws inserted in each patient [29], about 22 patients are needed in each group. A forward calculation demonstrates that for these sample sizes, and with the same accuracy as described above, a p-value of 0.006 will be returned.

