### Statistical analysis

In order to evaluate hypotheses of variables in contingency tables, the Chi-square or Fisher's Exact Tests will be used as appropriate. In order to test differences in continuous variables measured on at least interval scale between two independent groups the Student’s t-test for uncorrelated means will be used. The non-parametrical Mann–Whitney test will be used to test ordinal data. Regression analysis will be used to evaluate the dependency between variables and the Pearson correlation coefficient will be used in order to test independence between variables. In addition to that descriptive statistics will be used to characterize the data; means and 95% confidence intervals will be used for parametric data, medians and interquartile ranges for non-parametric data, and number (proportions) for categorical data. In case of multiple groups comparison. ANOVA, Kruskal–Wallis, and Chi-squared tests will be used respectively, along with post hoc analysis.

Protocol deviations will be recorded transparently. However, data from the different groups will be compared based on the'intention to treat'principle. An intention to treat (ITT) analysis means that all patients, regardless of treatment change, loss to follow-up or drop-out, remain in the analysis of the group to which they were randomized.

Statistical expertise will perform the statistical analysis.

Patient reported outcome measures consisting of ordinal scales for the different indices, will be compared using the Mann–Whitney test.

Data on total time on sick leave as well as the diagnosis used for sick leave will be collected.

Data on analgesic and antibiotic use will be collected from hospital files. Since different opioids may be used, conversion to morphine equivalents may be done. Data on other analgesics will be collected. Data on costs for the prescribed pharmaceuticals will be collected. Total amount of collected opioids (continuous data consisting of morphine equivalents) will be compared with the Student’s t-test or the Mann–Whitney test, depending on distribution.

Adverse events will be collected during the follow-up and classified as minor or major [30]. Data will be analyzed as dichotomous variables with Chi-square or Fisher tests.

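### Three primary comparisons, one of them sized at full alpha: the protocol does not say which contrast decides, or whether the three-group test gates the pairwise tests

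*Protocol article*

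**What the plan says.** - **Comparisons.** The section on outcomes and variables states: "Primary and secondary study outcomes will be studied in comparisons between ARSN and free hand, IRSN and free hand, and ARSN and IRSN". The sentence covers the primary endpoint and gives no order and no alpha.
- **Aim.** The abstract says: "The aim of this trial is to compare AR and conventional surgical navigation to free-hand technique". The Introduction likewise sets out to "compare conventional and AR surgical navigation to free-hand technique based on three main study domains". Both describe navigation against FH. The title and the abstract's design paragraph describe a three-way comparison.
- **Sizing.** Sample size for primary objective assumes that "accuracy at 1 st attempt in any of the navigated groups is p_nav_ = 91" per cent and that "accuracy in the free hand group is p_control_ 84" per cent. It continues: "Consequently, a one-sided test can be used", and then: "With a power of 80%, alpha = 0.05, a sample size of 301 screws is obtained". One rate serves both navigation systems, so no difference between ARSN and IRSN is planned for.
- **Analysis.** The Statistical analysis section lists two-group tests and adds: "In case of multiple groups comparison. ANOVA, Kruskal–Wallis, and Chi-squared tests will be used respectively, along with post hoc analysis". This is a general sentence. It does not name the primary endpoint or a post hoc method, and it does not make pairwise testing conditional on the three-group result.

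**The concern.** The comparisons section, the sizing and the analysis section do not describe the same test. The first gives three primary contrasts equal standing. The second spends the whole one-sided 0.05 on a single contrast. The third offers a three-group test with no direction, which is not the one-sided pairwise test that was sized.

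As written, a positive primary result could be claimed from ARSN vs FH, from IRSN vs FH, from ARSN vs IRSN or from the three-group test. These can disagree, and the protocol does not say what disagreement would mean. At stake are the false-positive rate behind the trial's main claim and the freedom to choose the emphasis once the data are seen.

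**Working it through.** **1. What the stated sample size covers.** Inputs from Sample size for primary objective: 0.91 and 0.84, one-sided alpha 0.05, power 80%, continuity correction, equal groups.

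- Uncorrected: n0 = (1.645 + 0.842)² × (0.84×0.16 + 0.91×0.09) / 0.07² = 6.183 × 0.2163 / 0.0049 = 272.9.
- Corrected: n = (n0/4) × [1 + √(1 + 4/(n0×0.07))]² = 68.2 × (1 + √1.2094)² = 300.8, so 301, as stated. The pooled-variance formula gives 303.
- 301 × 1.1 = 331.1, so 332; 332/15 = 22.1 patients. Both match.

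The 301 is therefore one contrast at the full one-sided 0.05. With pooled variance and continuity correction, a two-sided test, or a one-sided test at 0.05/2, would need 378 per group.

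**2. Ungated pairwise tests, no true difference between arms.** Screws are treated as independent, as in the sizing. With three equal arms the two FH contrasts share the FH arm, so their correlation is (1/n)/(1/n + 1/n) = 0.5.

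| Tests at 0.05 each | At least one false positive |
|---|---|
| Two vs FH, one-sided | 1 − Φ₂(1.645, 1.645; 0.5) = 8.8% |
| Two vs FH, two-sided | 9.1% |
| Two vs FH one-sided, plus ARSN vs IRSN two-sided | 12.3% |
| All three two-sided | 12.2% |

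The first row is exact and the others are simulated with 2 million normal draws. Binomial simulation at 301 and 332 screws per arm gives 8.9–9.0% for the first row and 11.9–12.3% for the last. The independence formulas, 1 − 0.95² = 9.75% and 1 − 0.95³ = 14.3%, overstate because the contrasts share arms.

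**3. The same tests behind a gate.** If the two-sided pairwise tests run only after a three-group chi-squared test (2 degrees of freedom) is significant at 0.05, the simulated rate is 5.0%. With exactly three arms this also holds when one arm truly differs: at most one pair is then still equal, and it is tested once at 0.05.

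**4. Sensitivity to arm layout.** The randomization section gives a 1:1 ratio stratified by theatre, with the two systems in different theatres. The secondary sample size section pools to 44 navigated and 44 FH patients. An FH group twice the size of each navigated arm is therefore possible. The ungated rates then become 9.2% (two one-sided), 12.4% (adding ARSN vs IRSN two-sided) and 12.1% (three two-sided). Separate FH controls for each system give 9.75% for the two FH contrasts. The error rate barely depends on layout.

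**5. Power per FH contrast.** Binomial simulation, three equal arms of 301 independent screws, chi-squared test without continuity correction (hence 83% rather than 80% at the start).

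| Rule | Both systems at 91% | Only one at 91% |
|---|---|---|
| One-sided 0.05, no adjustment | 83% | 83–84% |
| One-sided, Holm over two contrasts | 80% | 75% |
| Two-sided 0.05, no adjustment | 75% | 75% |
| Two-sided, behind the three-group gate | 70% | 68% |

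**6. Disagreement between the two FH contrasts, both systems at 91%.** These figures do depend on layout (one-sided / two-sided).

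| FH layout | Verdicts differ | Both significant |
|---|---|---|
| One shared arm of 301 screws | 19% / 26% | 74% / 62% |
| One shared arm of 602 screws | 13% / 21% | 85% / 74% |
| Separate FH arms of 301 screws | 28% / 38% | 70% / 56% |

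**The case against.** The strongest reply is that this is an omission from a journal article. Testing order and post hoc method usually sit in an SAP, which is not shown, and the listed three-group test can naturally be read as coming first. Much of this stands. A reader might infer that the trial's false-positive rate is 9–12%, or that the protocol has no multiplicity control at all. The text does not support either as fact: gating is neither adopted nor excluded, and a gate would hold the rate at 5.0%. Nor does any section state an alpha for ARSN vs IRSN; 0.05 is inferred there.

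The reply does not remove the point, because the protocol itself fixes things that do not fit together. It names three primary contrasts and sizes one at the full one-sided alpha. An SAP that split alpha or used the non-directional gate would leave the stated 80% describing a different test.

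A second objection is that two distinct systems, each set against FH, answer separate questions and need no joint error control. That view is defensible, but it has to be stated, and it would not settle the place of ARSN vs IRSN, which has neither a planned difference nor a sample size.

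A reader might also infer that the 80% is offered as power to show that both systems beat FH. The protocol makes no such claim, so the lower both-systems figures are not evidence of a misstatement.

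**Conclusion.** The point holds in conditional form. The protocol has three unranked primary contrasts, a sample size for one of them at undivided one-sided 0.05, and a three-group test whose role is not stated. Run ungated at 0.05, the pairwise tests carry about a 9% chance (two FH contrasts) or 12% chance (all three) of at least one false primary result; gated, 5.0%.

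These rates assume no true difference between arms and independent screws. Clustering of screws within patients is a separate matter that would raise the error of each test. The rates are stable across plausible arm layouts, whereas the disagreement and both-systems figures are not and should be quoted only with their layout. This should be corrected, and wording is enough to do it.

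**What to change.** Before database lock, state one rule, consistently, in Study outcomes and variables, Sample size for primary objective and Statistical analysis:

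- **Option (a).** The primary family is ARSN vs FH and IRSN vs FH, tested with Holm at overall alpha 0.05. A system is declared better than FH only if its Holm-adjusted test is significant. ARSN vs IRSN becomes secondary, reported as an estimate with a confidence interval. This keeps the one-sided direction used in the sizing.
- **Option (b).** All three contrasts stay primary, but the two-sided pairwise tests at 0.05 are run only if the three-group chi-squared test is significant at 0.05. This uses a test already listed.

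Then restate the power for the chosen rule and say how many FH screws it assumes.

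No extra patients are required; the cost is power per comparison. With three equal arms of 301 independent screws, Holm takes it from 83% to 80% if both systems work and to 75% if only one does. The gate takes two-sided power from 75% to 70% if both work and to 68% if only one does. Measured against the one-sided test that was sized, option (b) costs more (83% to 70% or 68%), because part of the loss comes from moving to two-sided testing.

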#### Primary outcomes

The primary endpoint is accurately placed pedicle screws based on intraoperative verification scan by cone beam computed tomography (CBCT).

An accurately placed screw is defined as one that is placed with less than 2 mm cortical breach of the pedicle (corresponding to Gertzbein grade 0–1) [23].

The endpoint, accurately placed pedicle screws, is calculated as: the number of accurately placed screws (Gertzbein grade 0 + 1) according to intraoperative verification CBCT scan divided by the total number of placed screws.

Screws that are not placed and screws that are placed but repositioned before intraoperative verification CBCT scan are noted in the Case report form (CRF).

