### Randomization and blinding

The subjects are randomized in a 1:1 ratio, with stratification for operating theatre since the IRSN or ARSN system are located in different operating theatres. Randomization will take place intraoperatively after completed surgical exposure of the posterior elements and will be performed through the web-based platform of the Swespine registry using an allocation sequence hidden from the healthcare staff. Block randomization will be used. Block sizes will be unknown for the researchers.

The study design does not allow blinding of the surgeon. Since the primary outcome is assessed at the time of surgery and a short time thereafter, we do not find it necessary to blind the patient.

Intraoperatively, CBCT verification scans will be assessed by the surgeon to make decisions on screw revision. However, all radiological image analyses, on both intra- and postoperative imaging will be performed postoperatively by blinded reviewers.

Patient reported outcomes will however be assessed without influence of the care giver.

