#### Secondary outcomes related to implant density

Pedicle screw placement density comparison. The study aims for 100% pedicle screw density. Hooks may be placed as rescue or if screw placement fails.Final implant density compared to planned 100% pedicle screw density.Pedicle screw density.Hook density.Morphometric measurement for regression analysis.Pedicle diameters are measured on preop CT.Deformity correction rate.Cobb angle improvement.

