### Limitations

This trial has several limitations including the lack of a triple-blinded design, and the relatively small sample size which does not allow for full interpretation of secondary outcomes. In that aspect, although blinding does not affect any of the primary outcomes of this trial, it may potentially influence the secondary outcomes, especially PROMs, which constitutes a noteworthy limitation. Also, the trial will be conducted in a single country and at a single center, with surgeries being performed by highly experienced spine surgeons, which hampers generalizability of the findings.

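### The primary endpoint counts only placed screws, so pedicles left without a screw before the verification scan leave the accuracy comparison, and the arms may omit different numbers

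*Protocol article*

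**What the plan says.** All places are in the protocol article.

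- **Primary outcomes.** The endpoint is the count of Gertzbein grade 0–1 screws "according to intraoperative verification CBCT scan divided by the total number of placed screws". For the rest: "Screws that are not placed and screws that are placed but repositioned before intraoperative verification CBCT scan are noted in the Case report form". They have no stated role in the numerator or the denominator.
- **Secondary outcomes related to accuracy.** First-attempt accuracy and final accuracy also divide by the total of placed screws.
- **Secondary outcomes related to implant density.** "The study aims for 100% pedicle screw density. Hooks may be placed as rescue or if screw placement fails". One listed outcome is "Final implant density compared to planned 100% pedicle screw density"; screw density and hook density are listed separately.
- **Randomization and blinding.** Allocation takes place during surgery, once the posterior elements are exposed and therefore before any screw is placed. "The study design does not allow blinding of the surgeon". The image readers are blinded.
- **Abstract, Background and purpose.** Of navigation, the authors say that it "allows placement of pedicle screws in small and deformed pedicles and may result in both a higher accuracy and density of pedicle screw placement".
- **Limitations.** The authors write that "although blinding does not affect any of the primary outcomes of this trial".

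**The concern.** With a 100% density target, each pedicle in the construct is an intended screw. Which of them receive a screw is settled after allocation, by a surgeon who knows the arm. The arms also decide on different information: navigated screws are planned on a three-dimensional scan, free-hand screws rely on landmarks and feel. The denominator is therefore a post-randomisation quantity that treatment can change.

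If one arm leaves more difficult pedicles empty, its remaining screws are an easier set and its accuracy rises without any better placement. The authors' own expectation of higher density with navigation makes unequal omission plausible. In that direction it would understate a navigation advantage. If planning on the scan led instead to more omission under navigation, it would overstate one. Blinded reading does not help, because readers can grade only the screws that are present.

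**Working it through.** **1. Reproduce the protocol's own figure.** Inputs from Sample size for primary objective: 91% and 84%, one-sided alpha 0.05, power 80%, continuity correction, equal groups.

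- n0 = (1.645 + 0.842)² × (0.84×0.16 + 0.91×0.09) / 0.07² = 272.9.
- With continuity correction: n0/4 × [1 + √(1 + 4/(n0×0.07))]² = 300.8, so 301 as stated. The pooled-variance version gives 303.
- 301 × 1.10 = 331.1, rounded up to 332. 332/15 = 22.1 patients.

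**2. Assumptions for omission.** The documents give no omission rate. Let x be the share of free-hand target pedicles left without a screw at the verification CBCT, and f the share of those that would have breached had a screw been placed. Assume 91% (navigated) and 84% (free hand) accuracy if every target pedicle were instrumented, 332 target pedicles per arm, and no omission in the navigated arm. Screws are treated as independent, as the protocol's calculation does.

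**3. Observed free-hand accuracy among placed screws** = (0.84 − x(1 − f)) / (1 − x). It rises above 84% whenever f exceeds 16%, the arm's underlying breach rate.

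At x = 5%, 332 × 0.95 ≈ 315 free-hand screws remain:

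- f = 30%: 0.805/0.95 = 84.7%; observed difference 6.3 points.
- f = 50%: 0.815/0.95 = 85.8%; observed difference 5.2 points.
- f = 100%: 0.840/0.95 = 88.4%; observed difference 2.6 points.

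**4. Power** = Φ[(difference − 1.645 × SE0)/SE1], with SE0 the pooled and SE1 the unpooled standard error, no continuity correction.

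- No omission: (0.0700 − 1.645×0.0257)/0.0255 = 1.09, power 86%.
- f = 30%: (0.0626 − 1.645×0.0256)/0.0256 = 0.80, power 79%.
- f = 50%: (0.0521 − 1.645×0.0251)/0.0252 = 0.43, power 67%.
- f = 100%: (0.0258 − 1.645×0.0239)/0.0239 = −0.56, power 29%.

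**5. Omission that would erase the 7-point difference:** x = 0.07/(f − 0.09). This is 7.7% at f = 100% (about 1.2 of 15 screws per patient), 17% at f = 50% and 33% at f = 30%.

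**6. The opposite direction.** If both arms are truly at 84%, only the navigated arm omits and every omitted pedicle would have breached, the one-sided rejection rate is 24% at 3% omission and 49% at 5%, against a nominal 5%. This is the extreme of f.

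**7. What a target-pedicle denominator would show in step 3.** Counting empty pedicles as not accurately instrumented, free hand scores 0.95 × 84.7% = 80.5%, 0.95 × 85.8% = 81.5% and 0.95 × 88.4% = 84.0%. The differences from 91% are 10.5, 9.5 and 7.0 points. Only at f = 100% does this return the 7 points of step 2. At lower f it is wider, because it also penalises leaving empty a pedicle that could have taken an accurate screw. It answers a different question and is a companion to the primary, not a corrected version of it.

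**The case against.** **Omission is already measured.** Not-placed screws go into the CRF, and density against the 100% target is a secondary outcome. An arm that skips pedicles would show lower density. This stands as mitigation, but only in part: nothing ties the density result to the reading of the accuracy result, so a distorted primary could be reported alone.

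**Per-placed-screw accuracy is a legitimate measure.** A misplaced screw and an empty or hooked pedicle are different events, and merging them rewards attempting doubtful pedicles. This stands, and is the reason to keep the primary as it is.

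**A supplementary analysis may belong in an unseen analysis plan.** True of its details. The denominator itself, however, is fixed in this document, and so is the Limitations remark.

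**The size is assumed.** It is. The large losses need omission in one arm only and nearly every omitted pedicle a breach. At f = 30%, 5% omission costs 7 points of power.

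A reader might also infer two things that the text does not support. The first is that the intention-to-treat principle is broken. The Statistical analysis section defines it for patients, who all stay in their randomised group; no screw-level version is promised. The second is that any screw extracted or replaced by a hook drops out. The intervention sections describe repositioning and extraction after the verification CBCT, and the primary is graded on that scan, so those screws still count. Only pedicles without a screw at that scan are lost.

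**Conclusion.** The point holds in a limited form. The primary endpoint conditions on a quantity that is determined after randomisation and may differ by arm. Neither blinded reading nor patient-level intention to treat removes this. Bias arises only if omission differs by arm and falls on pedicles more likely to breach than average. The protocol makes this plausible, not certain, and does not settle its direction.

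Under the stated assumptions, 5% omission in free hand alone would leave power anywhere between 29% and 79%, against 86% without omission. These are illustrations, not forecasts. The documents do not support saying that the result will be reversed, or that free hand will benefit. The Limitations statement is too strong as worded: outcome grading is protected by blinded readers, but the unblinded surgeon decides which screws exist to be graded.

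**What to change.** - Keep accurate screws per placed screw as the primary endpoint.
- Prespecify one companion (sensitivity) analysis, by the same method, with all pedicles in the 100%-density target as the denominator. Count any pedicle without a screw at the verification CBCT as not accurately instrumented. Do not take the target set from the navigation plan, which is drawn after allocation.
- Report this result and the omission rate by arm next to the primary, and interpret the accuracy finding in their light. Do not add a formal rule that both must agree: it could not restore a navigation advantage diluted by free-hand omission, and would only make the claim harder.
- Reword the Limitations sentence to say that image grading is blinded but that the surgeon's knowledge of the arm can influence which screws are placed.

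Cost: one extra analysis on data the CRF and density outcomes already capture. It mixes omission with breach, so it needs a sentence of explanation. No interim analysis is planned and analysis follows database lock, so it can be fixed beforehand as long as the database is still locked to analysis.
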